## 6.2 Control Product Description

BLES® is available in 3 and 5 ml vials for this trial. The vials are stored in a -20 degrees Celsius freezer for long term storage. A two month supply will be thawed and kept in the refrigerator, so that both study drugs will come from the same storage conditions in order to maintain blinding procedures. The drug, once thawed is opaque and milky in appearance.

## 6.3 Formulation, Packaging, and Labeling

Curosurf® is manufactured and provided by Chiesi Farmaceutici S.p.A. A detailed Product Monograph is found in Appendix F. The vials will be labeled for investigational study use. The commercial label will not be present. The vials will be shipped and stored between +2 and +8 degrees Celsius. There are two vial sizes for the study 1.5 mls and 3.0 mls.

The label applied on the vial will contain the following information:

| Curosurf-01  Poractant alfa 80 mg/mL - X mL  Expiration: DD-MMM-YYYY  Store in refrigerator between +2°C and +8°C, protected from light  Lot # -------  Protocol Code: ----------  Sponsor: The Ottawa Hospital, [name]  Investigational drug to be used only by a qualified Investigator | Curosurf-01  Poractant alfa 80 mg/mL - X mL  Expiration: DD-MM-YYYY  Conserver au réfrigérateur entre +2°C et +8°C, à l’abri de la lumière  Lot # -------  Code du Protocole: ------------  Commenditaire: The Ottawa Hospital, [name]  Médicament expérimental à être utilisé seulement par un Investigateur qualifié |
| --- | --- |

BLES® is manufactured by BLES Biochemicals Inc. A detailed Product Monograph is found in Appendix G. A dedicated stock of 3 and 5 ml vials will be secured by the sponsor. The vials will be relabeled using the template as below.

| Curosurf-01  BLES- X mL  Expiration: DD-MMM-YYYY  Store at -20°C for long term and then may be thawed and stored at +2°C to +8°C  Lot # -------  Sponsor: The Ottawa Hospital,  [name]  Investigational drug to be used only by a qualified Investigator | Curosurf-01  BLES- X mL  Expiration: DD-MM-YYYY  Conserver au congélateur à long-terme à -20°C et peut ensuite être dégelé et conservé de nouveau entre +2°C et +8°C  Lot # -------  Commenditaire: The Ottawa Hospital,  [name]  Médicament expérimental à être utilisé seulement par un Investigateur qualifié |
| --- | --- |

## 6.4 Accountability Procedures and Storage

**Investigational Group-Curosurf**®- Vials will be stored between +2 and +8 degrees Celsius. The study medication will be received by the site pharmacy and a drug receipt form will be completed and sent back to the shipper. A two month supply of drug will be transferred to the NICU where it will be stored in a locked container.

**Control Group-BLES**®- The vials will be stored in a -20 degrees Celsius freezer in the study center Pharmacy. A two month supply will be thawed and kept in the refrigerator in the NICU, in a dedicated locked container, to avoid mixing with regular NICU stock. These will be clearly labeled with an “expires on ____” date, to avoid administering drug that has been at refrigerator temperatures over the allotted time.

For both study drugs temperatures will be monitored daily, both in the main pharmacy and in the NICU, capturing the minimum and maximum temperatures for the previous 24 hours. Detailed instructions for cold chain management are found in the Study Resource Manual.

Drug accountability forms will be completed in the pharmacy for the main stock and subject accountability forms will be completed as each vial is administered in the NICU. Please see the Resource Manual for further instructions for completing the Drug Accountability forms.

## 6.5 Subject Compliance with Study Medication/Intervention(s)

Not applicable for this study.

## 6.6 Concomitant Medications

Narcotics/opiods will be the only concomitant medications collected for this trial. Any medications in this category given within 6 hours of study medication initiation up to 6 hours post extubation will be recorded, except in case of an SAE (where all con meds for the SAE will be captured).

# Study Procedures/Evaluations

There are minimal study procedures for this trial. The length of participation varies for each infant, depending on the gestational age at enrollment, therefore the number of data collection time points will also vary. The baseline, randomization and assessments while on the ventilator are standard for all subjects but the number of follow up time points will vary. A Timetable of Events follows on a subsequent page for a summary of all the study time points and activities.

## 7.1 Screening

There will be no screening time point for this study.

## 7.2 Baseline time point and Randomization

The baseline time point will occur after the consent has been obtained and the infant’s status fulfills the inclusion criteria, and no exclusion criteria. The following procedures will occur:

- Physical exam (includes vital signs) (the infant will not be reweighed for study purposes, the weight will be taken from the medical history)
- Medical History
- Concomitant medication history

The infant can then be randomized into the study. Each infant will be allocated to receive either Curosurf® (study drug) or BLES® (control) in a 1:1 ratio using a computerized random-number generator. Twins or higher multiples will be randomized as individual patients. Randomization will be stratified by center and by GA category (24-26 weeks and 27-31 weeks), with random block lengths. Allocation will be concealed in sealed, opaque, sequentially-numbered envelopes, which will be opened by a Respiratory Therapist (RT) not involved in the care of the infant. This will occur only after intubation. The drug will be prepared by the RT. Blinding procedures will occur as per Section 6 of this protocol.

A maximum of 3 doses can be given over a 72 hour period post randomization. Infants not extubated and requiring ≥30% oxygen with radiological evidence of RDS can receive further dose(s) of surfactant. Similarly, infants who fail extubation and need to be reintubated (criteria in Appendix C) could receive further dose(s) of surfactant if they require ≥30% oxygen with ongoing radiological evidence of RDS. The same blinding method will be used for each dose of surfactant given and each dose of surfactant will follow the randomization sequence (i.e. once randomized, an infant will receive the type of surfactant that was given at randomization).

## 7.3 Assessments at 30 minutes, 6 hrs, 12 hrs, 24 hrs, 36 hrs, 48 hrs

Every infant will have an assessment starting at 30 minutes, next at 6 hours, 12, hours, 24 hours, 36 hours, and 48 hours, while still intubated. At these designated times the infant will be assessed to see if they can be extubated using the criteria listed below (also Appendix B).

Once the infant has been extubated then the assessments for extubation will no longer be performed. If at any point the infant fails extubation and needs to be reintubated, this information will be captured and recorded at the next time point for data collection.

**Extubation criteria**

Infants enrolled in the study will be extubated when they meet all of the following criteria:

1. rate on ventilator ≤40 per minute and
2. mean airway pressure ≤ 10 cm H20 and
3. fi02 ≤ 30%

At these time points, information about SAEs, ventilator parameters, and con meds will also be collected.

**7.3.1 Reintubation and further drug administration**

If an infant has failed extubation and requires reintubation, this information will be captured at the subsequent study timepoint. Further doses of surfactant can be given, if the maximum (3 doses) has not been already administered, up to a maximum of **72 hours** post randomization.

If the study Investigator deems that a subject needs further doses of surfactant beyond 72 hours post-randomization then this subject will be removed from the study and followed as per section 9.4 of this protocol.

## Week 2, Week 4 and Week 8

At weeks 2, 4 and 8 (if the infant has not been discharged) any information pertaining to SAEs (if within the 30 day follow-up for SAEs) and any extubation assessment data should be captured. If any infant that has been transferred to another institution the site must make every effort to follow the infant. This should be done in accordance with the local Ethics Boards guidelines and approval should be requested as necessary.

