## Study Endpoints

**Primary Endpoint**

The primary efficacy endpoint is that the patient is alive and extubated at 48 hours post surfactant administration. We hypothesize that Curosurf® will increase the proportion of infants alive and extubated within 48 hours after surfactant therapy.

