## 6.1 Study Medication Description

Study medication for this trial will be maintained in bulk supply format, the vials will not be individually numbered. For both Curosurf® and BLES®, the correct dose, which is weight based, will be calculated by the study Investigator and the RT will be responsible to double check the calculation. Either study drug is given by endotracheal method within 48 hours of life. Repeated doses may be given, up to a maximum of 3. If further doses are required then open label BLES® should be administered. The doses should not be given more frequently than every 6 hours.

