## 8.2 Statistical Methods

Demographic and clinical characteristics of patients at baseline will be summarized by treatment group. Continuous variables will be summarized using mean, standard deviation, median, and interquartile range, as appropriate. Discrete variables will be summarized using frequency and percent. Analysis of the primary outcome will use logistic regression, with treatment group as the main independent variable, and adjusting for the stratification variables, centre and gestational age category. The intention to treat principle will be followed. Secondary analyses will include comparison of mortality rates by treatment group using a similar logistic regression model. Use of oxygen at 36 weeks will be analyzed similarly. Cox regression will be used to compare duration of ventilation by treatment group, adjusting for centre and gestational age category. Duration of oxygen support will be analyzed similarly. Durations for any patients who die while still on ventilation will be treated as censored values. Incidence of adverse events by treatment group will be summarized descriptively.

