## 9.4 Treatment Discontinuation

The criteria for permanent discontinuation of further study product/interventions for an individual subject are as follows:

- Completion of treatment/intervention as defined by the protocol
- Clinical reasons believed to be life-threatening by the physician
- SAE occurring during and shortly after administration of the study drug

The infant will continue to be followed with the parent’s/LAR’s permission if the study treatment/intervention is discontinued. There will be no changes to the follow-up time point schedule, except no study treatment/intervention will be administered.

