## 9.6 Protocol Violations/Deviations

Protocol violations/deviations will be reported by all study sites. Each site will keep a log of protocol violations/deviations that will be compiled at the end of the study. Each site will be responsible to report violations and deviations to their respective REBs, as per local requirements.

If any subject receives the incorrect study drug, this information will be reported to the sponsor.

If an infant requires more than one dose of study medication and it is discovered that the incorrect drug has been dispensed then this will be reported. The infant will be removed from the study but will be followed until the last timepoint of the study for safety reasons.

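### Sections 7.3.1 and 9.6 take some randomized infants out of the study after post-randomization events, at odds with the intention-to-treat statement in 8.2

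*Protocol*

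**What the plan says.** Two rules in the protocol end an infant's place in the study because of something that happens after randomization.

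- **Section 7.3.1** applies when the investigator judges that an infant "needs further doses of surfactant beyond 72 hours post-randomization then this subject will be removed from the study". The full clause adds a reference to follow-up: "this subject will be removed from the study and followed as per section 9.4 of this protocol".
- **Section 9.6** concerns dispensing errors. Any wrong-drug case is reported to the sponsor. If the infant needs more than one dose and the error is discovered, a further consequence follows: "The infant will be removed from the study but will be followed until the last timepoint of the study for safety reasons".

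Three other places bear on these rules.

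- **Section 8.2**: "The intention to treat principle will be followed".
- **Section 9.4**, to which 7.3.1 refers, is headed Treatment Discontinuation. With the parent's permission the infant continues in follow-up: "There will be no changes to the follow-up time point schedule, except no study treatment/intervention will be administered". Leaving the study is dealt with separately, in section 9.5.
- **Section 6.1**, after setting the maximum number of study doses, says: "If further doses are required then open label BLES® should be administered". It does not mention removal.

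**The concern.** Intention to treat means that every randomized infant is followed and analysed in its assigned group, whatever treatment it later receives. Both rules, read literally, break that after an event linked to the infant's respiratory course or to the drug received.

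Under 7.3.1 the affected infants are those with persisting disease beyond 72 h. If a site stopped collecting their data, or an analyst dropped or censored them at that point, the loss would be informative for duration of ventilation and oxygen, BPD or oxygen use at 36 weeks, and death before discharge. The Cox models in 8.2 would then censor infants because they were doing badly.

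Under 9.6 two infants with the same dispensing error are treated differently. The one who needs a single dose stays in, and the one who needs a second dose is taken out. That selects on poor response and on treatment received. Need for additional doses is itself a secondary endpoint.

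**Working it through.** **1. The plan's own figure.** Inputs from section 8.1: 44 per group, 5% type I error (two-sided assumed, since sidedness is not stated), and 40% on BLES against 69.3% on Curosurf. Power = Φ{[d − 1.96·√(2·p̄·q̄/n)] / √[(p1·q1 + p2·q2)/n]}, where p̄ = 0.5465 and d = 0.293. This gives [0.293 − 1.96 × 0.1061] / 0.1014 = 0.84, so power is 79.9%. The four table rows give 79.9% to 80.1%, so the table reproduces. For a full 30-point difference, power is 81.9%, 83.1%, 85.2% and 88.0% at control rates of 40%, 45%, 50% and 55%. If all infants are analysed as randomized, none of this changes.

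**2. Timing of the 7.3.1 rule.** The endpoint is fixed in section 4.2: "The primary efficacy endpoint is that the patient is alive and extubated at 48 hours post surfactant administration". I take the clock to start at the first dose, as the assessment schedule in 4.1 implies. With the ±2 h window, the endpoint is read at most 50 h after dosing. On opening the allocation envelope, section 7.2 says: "This will occur only after intubation". The drug is then prepared, so the randomization and dosing clocks start close together. The trigger lies beyond 72 h after randomization, and 72 − 50 = 22 h. Unless dosing came more than about 22 h after randomization, the primary outcome is recorded before removal is possible. The endpoints read later are still exposed.

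**3. Timing of the 9.6 rule.** Section 6.1 allows doses as little as 6 h apart, so a second dose can come well before 48 h. Section 7.2 reserves repeat doses for infants still intubated, or reintubated, who need at least 30% oxygen and have radiological RDS. Such an infant is not extubated at that moment and is more likely than others to fail the primary endpoint, though not certain to. Section 9.6 does not refer to 9.4, and the only stated reason for continued follow-up is safety.

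**4. Overlap of 6.1 and 7.3.1.** An infant who has had three doses and needs another after 72 h falls under both sections. One provides open-label BLES and is silent on removal; the other removes.

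**5. Size if removed infants were dropped from the primary analysis.** The documents give no counts or shares, so all of these are assumptions. Every removed infant is taken to be a 48 h failure.

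| Scenario | Calculation | Result |
|---|---|---|
| No true effect, 22/44 per arm, 1 removed from one arm | 22/43 − 22/44 | +1.2 points |
| Same, 2 removed | 22/42 − 22/44 | +2.4 points |
| Same, 5 removed | 22/39 − 22/44 | +6.4 points |
| 22/44 against 30/44 (true +18.2), 2 and 5 removed | 30/39 − 22/42 | +24.5 points |
| 40% against 69.3%, 5% removed in both arms | 0.693/0.95 − 0.40/0.95 | 30.8 points instead of 29.3 |
| 40% against 69.3%, 10% of BLES arm and none of Curosurf arm removed | 0.693 − 0.40/0.90 | 24.9 points; power 63.5% |

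The bias can go either way. It favours whichever arm loses the larger share of its failures.

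**The case against.** A reader might infer that the worst responders leave the efficacy data, so that the primary and every respiratory secondary endpoint is biased. The documents do not support that.

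- The 7.3.1 sentence goes on to keep these infants in follow-up under 9.4. Stopping treatment while following the infant is compatible with intention to treat.
- The 72 h trigger normally comes after the primary outcome has been recorded. Bias there would need recorded outcomes to be deleted, and no section says that they are.
- An infant extubated at 48 h and later reintubated could also meet the 72 h trigger, so those removed need not all be primary failures.
- Section 1.1 reports less redosing with Curosurf than with Survanta, not BLES, and section 1.2 says no published study compares Curosurf with BLES. A difference in removals between arms is possible but not shown.
- Section 9.6 needs a site error before it applies at all, and even then the infant is followed to the last timepoint.
- Sections 6.1 and 7.3.1 may be complementary, one setting a dose limit and the other a time limit.

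All of this stands as a limit on the size of the problem. It does not settle the wording. Removal in 7.3.1 and unchanged follow-up in 9.4 cannot both describe the same infant. The arguments about the 9.4 reference and the 72 h timing do not reach 9.6. Analysis sets may be defined in a statistical analysis plan not seen here, but that would not stop a site from acting on the protocol's instruction to remove an infant.

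**Conclusion.** The point holds as a conflict between the two removal rules and the intention-to-treat statement, with a further internal inconsistency in 7.3.1.

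- **7.3.1:** as timed, no effect on the primary endpoint or its power, provided dosing follows randomization within about 22 h. The exposure is informative loss from endpoints read after 72 h, and only if removal is taken literally. The documents give no expected number of such infants.
- **9.6:** the more serious rule in principle, because it can act before 48 h, depends on needing a repeat dose, and protects follow-up for safety only. In practice its effect is probably small: about 1.2 points for each primary failure dropped from an arm at 22 of 44, under the assumptions shown.

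The larger figures in the table illustrate a mechanism and do not estimate bias in this trial. The detectable rates in 8.1 sit at about 80% power with all 44 infants per group, so the table leaves no margin for exclusions.

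**What to change.** In sections 7.3.1 and 9.6, replace the removal wording with a statement that the infant stays in follow-up on the unchanged schedule for all efficacy and safety endpoints, subject to parental permission as in 9.4, and is analysed in the group to which it was randomized. Give single-dose and multi-dose wrong-drug cases the same analysis status. Any exclusion of wrong-drug cases belongs only in an additional per-protocol sensitivity analysis, alongside the intention-to-treat analysis.

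Sections 6.1, 7.3.1, 9.4 and 9.6 should also be reconciled on what happens when surfactant is needed beyond the study-drug limits or after a dispensing error. The clinical rule is for the sponsor to decide; the point here is only that the sections agree.

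The cost is about two sentences in a protocol amendment, plus the reconciliation. Both groups of infants are already followed, so the one practical addition is to make sure that efficacy data, and not only safety data, are collected for infants covered by 9.6.

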## Discharge home or discharge from the NICU admitting unit

This time point can occur at 36 weeks gestation or before. All SAEs con meds, extubation failure and secondary outcome assessments data will be captured (if not previously done). Any SAE information will be gathered and completed, unless the SAE has not resolved.

| Timetable of Events | | | | | | | | | | | |
| --- | --- | --- | --- | --- | --- | --- | --- | --- | --- | --- | --- |
| **Evaluation** | **Baseline** | **30 m.**  **(± 15 min)** | **6 hrs**  **(± 30 min)** | **12 hrs**  **(± 2 hrs)** | **24 hrs**  **(± 2 hrs)** | **36 hrs**  **(± 2 hrs)** | **48 hrs**  **(± 2 hrs)** | **Week 2**  **(±1 week)** | **Week 4**  **(±1 week)** | **Week 8***  **(±1 week)** | **Discharge from hospital**  **(36 wksGA)** |
| Consent 1 | X |  |  |  |  |  |  |  |  |  |  |
| Medical/Medication History | X |  |  |  |  |  |  |  |  |  |  |
| Physical Exam 2 | X |  |  |  |  |  |  |  |  |  |  |
| Demographics | X |  |  |  |  |  |  |  |  |  |  |
| Randomization | X |  |  |  |  |  |  |  |  |  |  |
| Ventilator parameters3 | X | X | X | X | X | X | X |  |  |  |  |
| Con Meds | X |  |  |  |  |  | X | X | X | X | X |
| SAE assessment |  | X | X | X | X | X | X | X | X | X | X |
| Extubation failure assessment |  |  |  |  |  |  |  | X | X | X | X |
| Secondary outcome assessment |  |  |  |  |  |  |  |  |  |  | X |

1 Consent may be obtained from the mother antenatally or after the birth of the infant.

2 Includes weight, Temperature (Axillary), heart rate (apical), respirations.

3 Includes Rate, PL-LP, PEEP, Pressure support, FiO2, Mean, Tidal volume, IT, and Flow

***** Data collection at this time point is not done if the infant has already been discharged.

.

# Statistical Plan

## 8.1 Sample Size Determination

Review of our data on duration of ventilation indicates that in 2010, 40% of patients meeting inclusion criteria were alive and extubated 48 hours after BLES®. We anticipate that the mean length of ventilation in the BLES® group will be similar or shorter in 2012. We therefore based our sample size calculation on the percentage of successful extubation within 48 hours in the BLES® group lying between 40% and 55%. Fixing the probability of type-I error at 5%, a sample of size of 44 per group will provide power in excess of 80% to detect an absolute difference of 30% in the percentage still intubated at 48 hours. (See Table)

| Percentage alive and extubated at 48 hrs | |  |  |
| --- | --- | --- | --- |
| BLES® group | **Detectable in Curosurf® group** | Risk difference | Relative risk reduction |
| 40% | **69.3%** | 29.3% | 0.488 |
| 45% | **73.9%** | 28.9% | 0.525 |
| 50% | **78.3%** | 28.3% | 0.566 |
| 55% | **82.3%** | 27.3% | 0.607 |

A recent RCT in a similar population found that 52% of infants who received Curosurf® were extubated by 48h compared to 22% of infants who received Survanta, an absolute reduction of 30% (15).

## 8.2 Statistical Methods

Demographic and clinical characteristics of patients at baseline will be summarized by treatment group. Continuous variables will be summarized using mean, standard deviation, median, and interquartile range, as appropriate. Discrete variables will be summarized using frequency and percent. Analysis of the primary outcome will use logistic regression, with treatment group as the main independent variable, and adjusting for the stratification variables, centre and gestational age category. The intention to treat principle will be followed. Secondary analyses will include comparison of mortality rates by treatment group using a similar logistic regression model. Use of oxygen at 36 weeks will be analyzed similarly. Cox regression will be used to compare duration of ventilation by treatment group, adjusting for centre and gestational age category. Duration of oxygen support will be analyzed similarly. Durations for any patients who die while still on ventilation will be treated as censored values. Incidence of adverse events by treatment group will be summarized descriptively.

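### The primary model adjusts only for centre and a two-level gestational age category; exact gestational age and pre-dose ventilator settings would add some precision at almost no cost

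*Protocol*

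**What the plan says.** Section 8.2 specifies logistic regression for the primary outcome (alive and extubated at 48 hours), with treatment as the main term and "adjusting for the stratification variables, centre and gestational age category". No other covariate is named.

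Section 7.2 defines the strata: "Randomization will be stratified by center and by GA category (24-26 weeks and 27-31 weeks), with random block lengths". Eligibility runs from 24+0 to 31+6 weeks, so the lower category spans three weeks and the upper one five.

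The Timetable of Events (section 7 and Appendix A) marks ventilator parameters at Baseline and at every assessment to 48 hours; its footnote includes rate, FiO2 and mean pressure. The baseline procedures in section 7.2 do not mention them. The extubation criteria in section 7.3 and Appendix B use rate, mean airway pressure and FiO2; the second reads "mean airway pressure ≤ 10 cm H20 and".

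Section 8.1 sizes the trial by an unadjusted comparison of two proportions with a 5% type I error rate. Its claim is that "a sample of size of 44 per group will provide power in excess of 80"%, the target being a 30-point absolute difference between the groups. For the control rate it assumes "the percentage of successful extubation within 48 hours in the BLES® group lying between 40% and 55"%.

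**The concern.** All infants from 27+0 to 31+6 weeks in a centre share one intercept, although readiness to extubate may well differ across those five weeks. The starting values of the three variables that later define readiness are scheduled for collection but are absent from the model. If these baseline variables predict 48-hour status, adjusting for them raises power and removes chance imbalance within the GA bands and in initial severity. In a trial of 88 infants with power close to 80% at the table's effect sizes, that is worth having. The choice must be made before unblinding, because covariates picked afterwards would not be credible.

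**Working it through.** **1. The plan's own figure.** Inputs from section 8.1: n = 44 per group, alpha 0.05 (taken as two-sided), control rates 40% to 55%, and the table's detectable rates. Allocation is "in a 1:1 ratio using a computerized random-number generator" (section 7.2). The pooled-variance formula without continuity correction is

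power = Φ{ [d√n − 1.96√(2p̄q̄)] / √(p₁q₁ + p₂q₂) }.

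For 40% vs 69.3%: d√n = 0.293 × 6.633 = 1.944; p̄ = 0.5465, so 1.96√(2 × 0.5465 × 0.4535) = 1.380; the denominator is √(0.240 + 0.2128) = 0.673. Hence Φ(0.838) = 79.9%. The four rows give 79.9%, 79.9%, 80.1% and 79.9%. A full 30-point difference gives 81.9% to 88.0% across the control rates. One-sided power would be about 88%, so the table rests on a two-sided test. The stated figure reproduces, and it takes no credit for covariates.

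**2. Effect of richer adjustment.** The protocol gives no prognostic strengths, so these are assumptions: GA log-odds 0 to 0.5 per week, and one standardized pre-dose ventilator score with log-odds 0 to 1.0 per SD, independent of GA. Further assumptions are GA uniform over 24 to 32 weeks, two centres, and stratified blocks of 2 and 4. Marginal rates were calibrated to the table's first and last rows. Tests were likelihood-ratio tests at 5%, with 2,000 simulated trials per scenario (Monte Carlo standard error about 0.8 points).

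Power (%): planned model → plus GA in weeks → plus ventilator score.

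| GA per week / score per SD | 40% vs 69.3% | 55% vs 82.3% |
|---|---|---|
| 0 / 0 | 80.5 → 80.8 → 80.2 | 82.4 → 82.4 → 81.6 |
| 0.2 / 0.3 | 82.5 → 82.6 → 83.2 | 81.5 → 81.8 → 82.3 |
| 0.3 / 0.5 | 80.9 → 81.6 → 83.7 | 81.5 → 82.3 → 84.9 |
| 0.4 / 0.7 | 85.4 → 86.4 → 89.0 | 85.0 → 85.8 → 89.1 |
| 0.5 / 1.0 | 86.1 → 87.7 → 91.8 | 86.1 → 87.0 → 91.7 |

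GA in weeks alone adds at most 87.7 − 86.1 = 1.6 points. The total change runs from 81.6 − 82.4 = −0.8 to 91.8 − 86.1 = +5.7 points. Up to a score effect of 0.7 per SD, the largest total gain is 89.1 − 85.0 = 4.1 points.

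A further simulation closer to the proposed model (three centres, two ventilator terms) gave at most about 1 point from GA in weeks and about 0 to 5 points from the full set. The loss was at most about 0.6 points when nothing was prognostic.

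**3. Type I error.** With 3,000 null trials in each of two scenarios, the planned model rejected in 4.8% to 5.0% and the richer model in 5.6% of both. The Monte Carlo standard error is √(0.05 × 0.95/3000) = 0.4 points, so 5.6% lies 1.5 standard errors above 5%.

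**4. Chance imbalance left by the plan.** In the simulation, the between-arm difference had an SD of about 0.28 weeks for mean GA and about 0.21 SD for the ventilator score. At 0.4 per week and 0.7 per SD, the 95% ranges on the log-odds scale are ±1.96 × 0.28 × 0.4 = ±0.22 and ±1.96 × 0.21 × 0.7 = ±0.29. The simulated treatment effect is about 1.6.

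**5. Effect scale.** For 45% vs 73.9% the risk difference is 28.9 points, the risk ratio 0.739/0.45 = 1.64 and the odds ratio (0.739/0.261)/(0.45/0.55) = 3.46. The design is stated on the first scale; the model's natural output is the last.

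**The case against.** The strongest reply is that nothing here is wrong. Adjusting for exactly the variables used in stratification is standard and valid. The promised power came from an unadjusted calculation, and the planned model reached at least 80.5% in every scenario. That stands: a reader might infer that the trial loses planned power, and the documents do not support this.

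A reader might also infer that uncorrected imbalance biases the result. It does not. Imbalance between centres and between GA bands is handled by stratification and adjustment; what remains averages to zero and is covered by the 5% error rate.

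The link to extubation is also weaker than it looks. The criteria apply to settings at the assessments from 30 minutes to 48 hours, not before dosing, and Appendix B allows physicians discretion. No figure in the protocol shows that pre-dose settings predict the outcome. Nor is their recording certain, since section 7.2 and the Timetable differ. GA in weeks is not listed as a data item, though eligibility to the day implies that it is known.

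Sparse data is a fair caution. At 55% vs 82.3%, expected failures number 44 × 0.45 + 44 × 0.177 ≈ 28. With two centres, five terms leave 28/5 = 5.6 failures per term, and more centres leave fewer. The simulations show little harm from this, so it argues for few covariates and does not defeat the change.

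Finally, section 8.2 does not say that only an odds ratio will be reported, so the plan cannot be faulted for omitting a risk difference.

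**Conclusion.** This is a missed efficiency of minor weight, not an error. The planned model is valid and meets its stated power. Richer adjustment would change power by about -1 to +6 points; most of any gain comes from the ventilator settings, and only if they are clearly prognostic. Replacing the two-level category by weeks of GA matters little by itself. These sizes rest on assumed prognostic strengths, uniform GA, a score independent of GA and correctly specified linear effects. The main simulation kept the GA category beside GA in weeks and used one ventilator score. The possible loss is under 1 point, so the balance favours the change. The mismatch between section 7.2 and the Timetable needs correcting in any case.

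**What to change.** Before unblinding, reword section 8.2 so that the primary logistic regression contains treatment, centre, GA at birth in weeks (continuous) and one or two pre-dose ventilator variables, FiO2 and mean airway pressure. Keep the model with centre and GA category as a sensitivity analysis. State how missing baseline settings will be handled. Add ventilator parameters to the baseline procedures in section 7.2 to match the Timetable, and make clear that they are taken before the first dose.

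Optionally, report a covariate-standardized risk difference with a 95% confidence interval beside the odds ratio, since the trial was sized on a risk difference.

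The cost is a few sentences, one to three extra model terms in 88 infants and a linearity assumption for GA. No additional data collection is needed if the Timetable is followed.
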